### Recruitment

Student recruitment and data collection began November 24, 2023, and is estimated to be completed by October 24, 2025, with results expected by January 24, 2026. Purposive and snowball sampling procedures will be used to recruit post-secondary students who are physically inactive and experiencing poor mental health. Post-secondary students will be recruited and referred to the intervention through the team’s research and professional networks (e.g., health and wellness and student support services; student life listservs; campus mental health listservs). Digital recruitment materials, including email templates and poster advertisements, will provide details about the purpose of the intervention, the procedures involved, eligibility criteria, and a link to the screening questionnaire. The purpose of this broad recruitment strategy is to enhance outreach and more effectively engage the diverse student population. Program reach will be examined to assess who is engaging with the intervention and how. These findings will offer valuable insights into potential disparities in uptake and help inform future strategies to improve accessibility, equity, and representation in program delivery. The screening questionnaire will be administered through REDCap [37] and will allow students to “sign up” up for the intervention by providing their email address and answering several questions to confirm eligibility. The program coordinator will contact eligible students to confirm their involvement in the study and to arrange an intake meeting.

### Statistical analyses

Prior to conducting the main analyses, descriptive statistics will be calculated for baseline demographic characteristics (e.g., gender, age, sexual orientation, ethnicity/race) and main study variables at each assessment point (T1, T2, and T3) across the trial arms. To assess baseline equivalence between trial arms, differences in demographic characteristics and main study variables at baseline will be examined using chi-square tests and one-way analysis of variance. Differences in dropout will also be examined based on demographic characteristics and baseline study variables using chi-square tests and independent samples t-tests. The absence of systematic differences in dropout would support the plausibility of the Missing At Random (MAR) assumption, which underlies the use of linear mixed effects modeling in handling missing data [36,78,79].

For the main analyses, linear mixed effects modeling will be used to examine intervention effects on the primary and secondary outcomes over time and model assumptions will be tested [36,79]. Model specifications are provided above for a priori sample size calculation purposes. Models will be estimated using restricted maximum likelihood with the *lme4* and *lmerTest* packages in R Version 2025.05.0 + 496. The intra-class correlation coefficient (ICC) will be reported to quantify the proportion of total variance in the outcome attributable to between-person differences, relative to within-person changes across timepoints. Significant interactions will be probed using within-group and between-group pairwise comparisons conducted with the *emmeans* package. *P* value and *95% CI* adjustments using Tukey method for comparing a family of 3 estimates will be used to adjust for multiple comparisons.

For the mixed methods process evaluation, quantitative closed-ended questions will be analyzed using descriptive statistics (means and standard deviations or frequency counts). Independent-samples t-tests and chi-square tests will be used to examine group differences between 1:1 and group delivery formats on process-related outcomes. Open-ended qualitative responses will be analyzed using thematic analysis [80]. An iterative coding process will be used, combining both an inductive (data-driven) and deductive (theory-informed) approach [81]. Findings from both quantitative and qualitative analyses will be integrated during interpretation in the discussion to provide a comprehensive understanding of student experiences and implementation processes.

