### Objectives and hypotheses

Using a type 1 hybrid effectiveness-implementation study design [22], this three-arm parallel randomized controlled trial (RCT) will evaluate the effects of 1:1 and group-based supervised PA, compared to a 10-week waitlist control, among post-secondary students across three timepoints: baseline (T1), post-intervention (T2; 6-weeks), and follow-up (T3; 1-month post-intervention). Primary outcomes will include the immediate changes (T1–T2) in mental health indices (i.e., anxiety, depression, psychological distress, and well-being). Secondary outcomes will include changes from baseline to follow-up (T1–T3) and maintenance effects from post-intervention to follow-up (T2–T3) in mental health indices, as well changes in social well-being indices (i.e., social connectedness, social support), and PA behavior. The aims of the study include: (1) examining group differences between 1:1 PA delivery, group-based PA delivery, and the 10-week waitlist control arm on the primary and secondary outcomes; and (2) grounded in process evaluation recommendations [24], to explore implementation outcomes (i.e.,., reach, adherence, acceptability, fidelity) that may be linked to variation in primary and secondary outcomes while offering insight for wider dissemination. Based on evidence supporting various PA modalities for improving mental health [25], both 1:1 and group-based PA are hypothesized to be more effective than the waitlist control on primary and secondary outcomes, with no expected differences between the PA conditions on primary outcomes. Drawing on the social identity approach to health [20], it is hypothesized that group-based delivery will result in greater improvements in secondary outcomes including social well-being outcomes and maintenance effects compared to 1:1 delivery. However, 1:1 delivery is expected to yield more favourable implementation outcomes, due to its potential for stronger individualized support [14,26]. The results will provide novel insight into the effectiveness of different PA program delivery styles on student mental health, social well-being, and PA behaviour, while also offering implementation considerations to support the sustainability and scale-up of PA interventions across post-secondary campuses.

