### Sample size

A simulation-based power analysis using the *simr* package in R was conducted [75]. This analysis estimated the likelihood of detecting a group-by-time interaction in a linear mixed model using restricted maximum likelihood. The simulated design included three groups (1:1 PA intervention, group PA intervention, and waitlist control), with primary and secondary outcomes assessed at three time points: pre-intervention (T1), post-intervention (T2), and follow-up (T3). The model included fixed effects for group, time, and their interaction, as well as a random intercept for students to account for within-subject correlations. A moderate treatment effect (*d* = .50) was applied at the post-intervention time point, and a smaller sustained effect (*d* = .20) was applied at follow-up. Simulated data included realistic between- and within-person variability, and the outcome variable was centered to aid model convergence. To reflect anticipated study conditions aligned with typical attrition in PA and mental health intervention research [76,77], the analysis included missing data at random in approximately 20% of observations, with a slightly higher dropout rate (30%) at the follow-up time point. All available data from each student will be used, aligning with an intention-to-treat analysis, and no ad hoc imputation will be performed, as researchers have suggested that linear mixed models without such imputation are more powerful than ad hoc strategies [78].

Based on 1,000 simulations, a total sample size of 114 students (~38 per group) yielded an estimated power of 98.10% (95% CI: 97.05, 98.85) to detect the group-by-time interactions using a Type II F-test with Satterthwaite degrees of freedom at α = .05. This high level of power reflects the modeled effect structure and supports the adequacy of the proposed sample size.

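### The primary outcomes are T1–T2 changes, but the plan never names the arm-versus-waitlist contrast in that change as the primary test, and reaches its pairwise comparisons only through a three-timepoint interaction test

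*Protocol article*

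**What the plan says.** **Objectives and hypotheses.** "Primary outcomes will include the immediate changes (T1–T2) in mental health indices"; T1–T3 and T2–T3 changes are listed as secondary. The directional hypothesis is that "both 1:1 and group-based PA are hypothesized to be more effective than the waitlist control on primary and secondary outcomes". The same sentence adds "with no expected differences between the PA conditions on primary outcomes". No margin is given for that last expectation.

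**Sample size.** "The model included fixed effects for group, time, and their interaction, as well as a random intercept for students". The test that was powered is the group-by-time interaction across all three time points. A standardized effect of .50 "was applied at the post-intervention time point, and a smaller sustained effect" of .20 was applied at follow-up. The stated power is 98.10% (95% CI 97.05 to 98.85) with 114 students.

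**Statistical analyses.** The main analysis takes over that model: "Model specifications are provided above for a priori sample size calculation purposes". Follow-up is conditional: "Significant interactions will be probed using within-group and between-group pairwise comparisons", with Tukey-adjusted p values and 95% CIs for a family of three estimates.

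**Allocation and blinding.** The article describes itself as the pre-specified plan that the analyses will follow. It also says that the investigators, who run the analyses, are not blinded.

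**The concern.** The question the trial puts first is whether each physical activity (PA) arm improves more than waitlist from T1 to T2. In the model this is one contrast per arm: the arm's T1–T2 change minus the waitlist's T1–T2 change. The analysis text does not name it. It names an omnibus test that mixes T2 and T3, then pairwise comparisons that are most naturally simple effects.

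- Comparing times within an arm does not compare arms.
- Comparing arms at T2 is a fair randomized comparison, but it is not the stated change. It is also less precise than the change contrast when repeated scores are strongly correlated.

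Two things are at stake: the power of the comparison that will actually be reported, which is not the comparison the 98.1% refers to, and room for choice among contrasts by unblinded analysts. A related risk concerns one-on-one versus group delivery. The plan has only difference tests for this comparison, reported only after a significant interaction, so a non-significant result could be taken as confirming the expectation of no difference.

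**Working it through.** **Inputs.** From Sample size: 38 per arm; effects .50 at T2 and .20 at T3, applied here to both PA arms and scaled to the total SD; about 20% of observations missing, 30% at follow-up. Assumptions: missingness of 0/20/30% at T1/T2/T3, and ICC from .5 to .887, because the variance components are not given.

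**Degrees of freedom.** (3 − 1) × (3 − 1) = 4. Two of these belong to T3.

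**The plan's own figure.** The exact binomial interval for 981 of 1,000 is 97.05 to 98.85, as printed. The power itself depends on the ICC. With complete data the noncentrality is

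λ = (2/3) × 38 × [2(.50²) − 2(.50)(.20) + 2(.20²)] / [3(1 − ICC)] = (2/3) × 38 × .38 / [3(1 − ICC)] = 3.21 / (1 − ICC).

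Power of 98.1% needs λ of about 23.2, so ICC is about .86. With 0/20/30% missing, the ICC that gives 98.1% is .887. At ICC .5, .7 and .8 the interaction test has about 42%, 64% and 83% power.

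**Precision of the two candidate contrasts.** With complete data, Var(difference in change) = 4(1 − ICC)/38 and Var(difference at T2) = 2/38. They are equal at ICC .5, and above that the change contrast is more precise. The standard errors with missingness are in the table.

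**Power for one PA arm against waitlist, true effect .50.**
- Change contrast, ungated, Dunnett critical value 2.21: 1 − Φ(2.21 − .50/SE). At ICC .5: 1 − Φ(2.21 − 2.016) = 1 − Φ(.194) = .42.
- Path as written: the 4-df test must be significant, then the T2 comparison must pass the Tukey critical value of about 2.36 (200,000 simulated trials per ICC).

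| ICC | SE, T1–T2 change | SE, T2 only | Gate then Tukey at T2 | Ungated Dunnett, change |
|---|---|---|---|---|
| .5 | .248 | .248 | 22% | 42% |
| .6 | .223 | .245 | 25% | 51% |
| .7 | .194 | .242 | 30% | 64% |
| .8 | .159 | .238 | 36% | 83% |
| .887 | .12 | .235 | 41% | 98% |

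The figures are good to about one percentage point.

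**Where the loss comes from.** At ICC .5 the two standard errors are equal, so the loss is due to the gate and to Tukey rather than Dunnett. Without the gate, the Tukey T2 comparison would have 1 − Φ(2.36 − 2.016) = 37%, against 22% with it. At ICC .887 the gate removes only 1–2 points; nearly all the loss comes from testing T2 alone instead of the change.

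**What the gate responds to.** With an effect only at T3 (assumed .50 SD), the interaction is significant in 46% to 87% of trials at ICC .5 to .8. A significant interaction is therefore not evidence of a T1–T2 effect. The Tukey T2 comparison behind it still rejects for a given arm in under 1% of such trials, so false-positive error on that comparison is not inflated.

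**One-on-one versus group, T1–T2 change.** The unadjusted 95% half-width is 1.96 × SE: 1.96 × .248 = .49 SD at ICC .5 and 1.96 × .12 = .24 SD at ICC .887. If the arms truly differed by .30 SD, the result would be non-significant about 77% of the time at ICC .5, 66% at ICC .7 and 29% at ICC .887.

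**The case against.** **The contrasts may be meant correctly.** Three arm-specific T1–T2 changes are also a family of three, and exact contrasts are often left to a separate analysis plan. If that is the intention, the gated Tukey change contrast has about 29/38/52/74/96% power at the five ICCs, and the shortfall against the ungated Dunnett test is much smaller. This stands as a possibility. But the text does not say so, within-group against between-group is the usual language of simple effects, and the article calls itself the pre-specified plan. The condition on a significant interaction is fixed in either case.

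**The T2 comparison is valid.** This stands. A reader might infer that the reported comparisons would be biased; they would not, since arms compared at T2 were randomized. The fault is a mismatch with the stated change and a loss of precision at high ICC.

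**The gate is nearly free on the sponsor's own assumptions.** This also stands, if the 98.1% rests on an ICC near .89. A reader might infer that the 98.1% is wrong; the document does not show that, because the variance components are not given.

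**No equivalence claim is made.** A reader might infer that the trial sets out to show the two PA formats are equivalent. The article states an expectation, declares no equivalence or non-inferiority aim, and does not say that non-significance will be read as support. Only a caution on interpretation is warranted.

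**Maintenance.** A reader might also infer that superiority over waitlist on T2–T3 change contradicts the assumed fall from .50 to .20. That relies on reading a blanket phrase about primary and secondary outcomes literally. The explicit maintenance hypothesis compares group with one-on-one delivery, and T1–T3 change is already a secondary outcome. The point is not pursued.

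**Conclusion.** The concern holds in a limited form. The arm-versus-waitlist difference in T1–T2 change, which is the primary question, is not named as the primary test. Follow-up is conditional on an interaction test that includes secondary data. On the natural reading, per-arm power runs from about 22% to 41% over ICC .5 to .887, against about 42% to 98% for a direct contrast. Even at the ICC that reproduces 98.1%, that figure does not describe the T2 comparison that would be reported.

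These sizes assume both PA arms share the planned effects, d is on the total SD, and missingness is 0/20/30%. The balance between gate and contrast shifts with the unstated ICC. For one-on-one versus group, a half-width of about .49 to .24 SD means a non-significant result could not by itself support the expectation of no difference.

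**What to change.** In Statistical analyses, before the data are analysed:

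1. Name as primary, for each primary outcome, two contrasts from the fitted model: one-on-one minus waitlist and group minus waitlist, each in T1–T2 change. Test them whether or not the interaction is significant.
2. Adjust the two by Dunnett. If one-on-one versus group is to stay in the adjusted family, use Tukey over the three arm-specific changes instead. That costs some power against waitlist: about 37% rather than 42% at ICC .5, and 96% rather than 98% at ICC .887.
3. Make the three-timepoint interaction test and the T3 contrasts secondary.
4. Report one-on-one versus group on T1–T2 change as an estimate with its 95% CI in all cases, and state that a non-significant difference will not be read as support for no difference.

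The cost is a few contrast lines in the existing *emmeans* code and some wording, with no new data. The article's Ethical considerations section already provides a route for documenting changes to analyses. The downside is a more cautious conclusion on one-on-one versus group delivery.

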**Methods and analysis:**

Post-secondary students who are physically inactive and experiencing poor mental health will be recruited. A 3-arm parallel Randomized Controlled Trial, using a hybrid effectiveness-implementation design, will be conducted using a collaborative implementation approach. The effects of 6-week supervised one-on-one and group PA, compared to a waitlist control will be examined, with outcomes assessed at baseline (T1), 6-weeks (T2), and 1-month follow-up (T3). Primary outcomes will include immediate post-program changes (T1–T2) in mental health indices, including anxiety, depression, psychological distress, and well-being. Secondary outcomes will include changes from baseline to follow-up (T1–T3) and maintenance effects from post-intervention to follow-up (T2–T3) in mental health indices, as well as changes in social well-being indices (i.e., social connectedness, social support), and PA behavior. A process evaluation will be conducted to explore contextual influences (i.e., fidelity, adherence, reach, acceptability) on the conduct of implementation across PA program delivery styles. Effectiveness data will be analyzed using linear mixed effects modeling. Process evaluation outcomes will be analyzed using a mixed methods evaluation.

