### Allocation and blinding

Simple randomization will be used to allocate eligible students to the intervention arms using Research Randomizer [www.randomizer.org; 34,35]. Each student will be individually randomized, with an equal chance of being assigned to any of the three groups (1:1 PA, group-based PA, or waitlist control). While simple randomization may lead to unequal group sizes, block randomization was deemed unsuitable due to the risk of generating groups not comparable on covariates [34]. Stratified randomization was not possible given the continuous nature of student enrollment [34]. To account for the potential group size imbalance, primary statistical analyses will use linear mixed effects modeling, which are robust to unequal sample sizes and unbalanced data [36].

To minimize selection bias, allocation concealment will be used by having an investigator who will generate and assign random group allocations only after students have completed enrollment and the baseline (T1) assessment. Random allocations will be generated in real-time and not stored in advance. Students will be partially blinded in that students will be unaware of the purpose of group allocation or study hypotheses but will know they were assigned to an intervention arm or the control arm. To prevent care provider bias, PA coaches from Sport and Recreation Services will also not be informed about the purpose of group allocation or the study hypotheses. Investigators will not be blinded due to their roles in program coordination and statistical analyses. Recruiting an external individual to manage randomization, program coordination, and analyses is not feasible given the scope of the study and availability of resources. Nonetheless, several steps will be taken to minimize bias. Allocation concealment will be maintained until after baseline assessment, and analyses will follow the pre-specified plan outlined in this protocol paper. Outcome measures include open-ended and standardized self-report items, completed by students through a secure online data capture platform [REDCap; 37] without direct investigator involvement. The study protocol is also pre-registered to support transparency and reduce the risk of selective reporting.

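### Four unranked primary outcomes are each tested at .05, and the only stated adjustment works inside one outcome's model, so error across the four is not controlled

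*Protocol article*

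**What the plan says.** The Abstract defines the primary endpoint set: "Primary outcomes will include immediate post-program changes (T1–T2) in mental health indices, including anxiety, depression, psychological distress, and well-being". Objectives and hypotheses repeats the same four. Neither place ranks them, forms a composite, or says whether one, some or all must succeed. The hypothesis is that "both 1:1 and group-based PA are hypothesized to be more effective than the waitlist control on primary and secondary outcomes".

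Sample size describes a model with group, time and their interaction plus a random intercept per student. The interaction is tested "using a Type II F-test with Satterthwaite degrees of freedom at α = .05". Statistical analyses carries this model over to the analysis: "Model specifications are provided above for a priori sample size calculation purposes". Follow-up testing is conditional: "Significant interactions will be probed using within-group and between-group pairwise comparisons". The next sentence contains the only multiplicity rule: "Tukey method for comparing a family of 3 estimates will be used to adjust for multiple comparisons".

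Allocation and blinding notes that the investigators are unblinded and run the analysis. Among the steps to limit bias it states that "analyses will follow the pre-specified plan outlined in this protocol paper".

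**The concern.** Tukey for a family of three handles the three arm comparisons at one time point, or the three time comparisons within one arm. Both families sit inside a single outcome's model. With four primary outcomes there are four such models, and no rule connects them.

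With no success rule, a reader of the results cannot tell whether one positive scale out of four confirms the primary hypothesis or is what chance would often produce. This matters more here because unblinded investigators do the analysis and the article relies on its pre-specified plan as a safeguard.

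**Working it through.** **Inputs from the protocol article.** Four primary outcomes (Abstract; Objectives and hypotheses). Interaction test at α = .05, about 38 students per arm, three arms, three time points, random intercept (Sample size). Pairwise tests only after a significant interaction, with Tukey for three estimates (Statistical analyses).

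**Assumed, because the article does not give them.** Between-outcome correlation 0 to .9; ICC (share of variance that lies between persons) .5 or .7 in the table below.

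**The plan's own figure.** Power of 98.10% from 1,000 simulations means 981 successes. The exact binomial interval for 981/1000 is 97.05% to 98.85%, as printed. The power itself cannot be reproduced because the variance components are not stated. It describes one interaction test at .05, not a set of four outcomes.

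**Independent outcomes.** P(at least one false interaction) = 1 − (1 − .05)^4 = 1 − .8145 = .185. The upper bound under any dependence is 4 × .05 = .20.

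**Correlated outcomes and the interaction gate.** Simulation under the complete null (no effect on any outcome at any time): 20,000 replicates, 38 per arm, complete data. Each cell gives the result at ICC .5 / ICC .7.

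| Correlation | Any false interaction | Interaction plus Tukey between-arm contrast at T2 | Interaction plus between-arm T2 or within-arm T1–T2 contrast |
|---|---|---|---|
| 0 | 18.4% / 18.1% | 3.0% / 2.2% | 8.4% / 7.9% |
| .3 | 17.9% / 17.9% | 2.9% / 2.3% | 8.3% / 8.0% |
| .5 | 16.4% / 16.3% | 2.8% / 2.0% | 7.8% / 7.5% |
| .6 | 14.6% / 15.0% | 2.5% / 1.9% | 6.9% / 6.6% |
| .7 | 14.0% / 13.4% | 2.6% / 1.8% | 6.8% / 6.1% |
| .8 | 11.7% / 11.9% | 2.0% / 1.6% | 5.7% / 5.5% |

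At correlation .9 the first column falls to about 10%. A separate run at ICC .6 and .8 gave 1.4–2.6% for the between-arm T2 column, and below 1% when the contrast had to favour PA over waitlist.

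**When the gate is open for another reason.** The interaction test spans T1, T2 and T3. If there is a real effect at T3 only, the interaction is truly non-null while every T2 between-arm contrast is still null. The four sets of Tukey contrasts at T2 then run at close to their ungated rate. Ungated, the chance of at least one false T2 contrast is about 10% at correlation .9 and 18–19% at 0. Allowing for the gate sometimes staying shut, the rate is about 8–19%, depending on the size of the T3 effect.

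**With a cross-outcome rule.** Holm's first step is .05/4 = .0125. For four independent tests at .0125, 1 − (1 − .0125)^4 = 4.9%. In simulation it is about 3–5% over correlation 0 to .9.

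**The case against.** The strongest reply is the gate. An omnibus interaction on four degrees of freedom has no direction, includes T3, and cannot by itself show that PA beat waitlist at T2. A reader might infer that a claim that PA improves mental health carries about three times the nominal error. Under the complete null the documents do not support that: with the gate and Tukey applied, a false between-arm T2 finding on any of the four outcomes occurs in about 1–3% of trials. This part of the objection stands. It fails when some interaction is real for a reason other than a T2 effect. It also does not fully cover within-arm T1–T2 contrasts, which the plan allows and which bring the rate to about 5–9%.

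The text should not be over-read in two other ways. Tukey is not confined to the three arms, since the same sentence covers time comparisons within an arm. Nor does the article claim that Tukey handles the four outcomes; the sentence follows directly on the pairwise comparisons and describes them.

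It can also be argued that four distinct scales may be reported one by one, that adjustment across them is debated, and that requiring all four to succeed would remove the inflation. These are defensible designs, but the article adopts none of them.

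Finally, a separate analysis plan might settle the matter. However, the article states a specific adjustment and commits the analysts to the plan it sets out, so this is a rule that falls short rather than a detail left for later.

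**Conclusion.** The point holds and should be fixed before analysis, though it does not invalidate the design. Four primary outcomes are each tested at .05, no rule says how many must succeed, and the stated adjustment does not reach across them.

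The size depends on what counts as a false finding:

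- **At least one false significant interaction:** 18.5% under independence, about 10–19% over correlation .9 to 0.
- **A false between-arm T2 finding, nothing real anywhere:** about 1–3%; about 5–9% if within-arm T1–T2 contrasts also count.
- **A false between-arm T2 finding when a T3-only effect is real:** about 8–19%.

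The correlation range is an assumption, as the article gives none. The simulations use complete data and equal arms of 38. A narrower range such as 14–19% would require the correlation to be no higher than about .7, which the article does not establish.

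**What to change.** Add a short rule to Statistical analyses. For each of the four primary outcomes, test the T1–T2 difference of each PA arm against waitlist, keep the within-outcome arm adjustment, and take the smaller adjusted p-value. Apply Holm across the four: the ordered p-values are compared with .0125, .0167, .025 and .05 (that is, .05 divided by 4, 3, 2 and 1). Make a primary claim only for outcomes that survive. Label secondary outcomes and all other time contrasts as supportive. Say whether a significant interaction is still required first; Holm limits the outcome-level error either way. This controls claims about outcomes. Naming the arm within a surviving outcome still rests on the within-outcome adjustment.

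The change needs no new data, and the article's Ethical considerations section already provides for documented changes to analyses. The cost is a stricter first threshold and lower power per outcome. Its size cannot be derived from the article because the variance components are missing. As an illustration for the interaction test with the stated effects and missingness, moving from .05 to .0125 lowers power from about 98–99% to 92–97% if the ICC is .9, and from about 78–83% to 55–66% if it is .8.
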